### Time

The begin time and end time of the CT colonography procedure will be noted. The begin time is defined as the moment the patient enters the CT scanner room after changing clothes. The end time is defined as the moment the patient leaves the CT scanner room after the CT scan has been performed. Additionally, the time from the start of the procedure until the end time of recovery is noted. The end of recovery is defined as the time that the first Aldrete score of 9 or higher is measured.

### Questionnaires

All patients scheduled for clinical CT colonography will receive patient information and an informed consent form. Along with these forms, a pre-procedural questionnaire is sent to assess the baseline characteristics and expectations:

• Baseline characteristics include: age, gender, marital status, ethnicity, and education

• Expectations include burden and pain of: the bowel preparation, intravenous cannula insertion, bowel insufflation, and the total procedure on a standard formatted 5-point scale (no pain, mild pain, moderate pain, severe pain, and very severe pain)

A post-procedural questionnaire is given 30 minutes after the procedure. This time is standardized because the time between the procedure and the questionnaire may influence the answers. This questionnaire is designed to assess the experienced burden and acceptability:

• Experience includes burden and pain of: the bowel preparation, intravenous cannula insertion, bowel insufflation, and the total procedure on standard formatted 5-point scale (identical to the pre-procedural form)

• Which aspect of the procedure was most painful or burdensome (bowel preparation, intravenous cannula insertion, rectal catheter insertion, bowel insufflation, turning on the examination table or symptoms after examination)

• Acceptance includes: if they would accept this as a method for population screening

Both the pre-procedural questionnaire and post-procedural questionnaire are based on questionnaires used in a previous CT colonography trial [4].

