#### Secondary objectives

To assess the difference in:

• Pain score in all insufflation positions (right and left decubitus, supine and prone) and the average pain score

• Pain and burden of all CT colonography aspects (bowel preparation with oral iodinated contrast and diet, cannula insertion, rectal catheter insertion, insufflation, positional change on table and period after the procedure), and total pain and burden of CT colonography

• Side effects of alfentanil during CT colonography including:

○ respiratory effects (apnoea, respiratory frequency, and blood oxygenation)

○ hemodynamics (heart rate and blood pressure)

• Procedure and recovery time

• The most painful and most burdensome aspect of CT colonography

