### Statistical analysis

SPSS version 16.0 is used for all statistical calculations. A P value of 0.05 is defined as significant. Baseline characteristics are summarized with descriptive statistics. For categorical data the numbers or proportions are given, for normal distributed data the mean and standard deviation and for not normal distributed data the median with percentiles.

Differences between the alfentanil group and the placebo group will be tested for significance. For the calculation of differences in pain scores per position, average, and the maximum pain score during the procedure will be calculated using an independent samples t-test.

Differences in burden of different aspects of the procedure as well as the total procedural burden will be calculated using a chi-square test. Differences in the most burdensome aspect will also be calculated using the chi-square test. Differences in procedural time and recovery time will be calculated using an independent samples t-test.

We will test the associations between the baseline characteristics (independent variables mentioned below) and pain scores. As we consider the pain scores as continuous data, for this approach we will perform linear regression analyses.

Univariate analyses will be performed with pain scores as dependent variable and the following variables as independent variables: age, sex, BMI, education, ethnicity, expected burden, scan indication (including abdominal pain), known diseases and diagnosis, and whether it is the first CT colonography. Subsequently, the variables with a P value < 0.1 will be included in the multivariate analysis. In case more than four variables turn out to result in a P < 0.1, the four most influential variables will be used in the multivariate analysis. A stepwise backward selection strategy will be used, with a P value < 0.05 considered statistically significant.

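### As described, burden is rated in categories that are all grades of pain, and one worst-aspect item joins most painful and most burdensome, so the burden results could merely repeat the pain result

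*Protocol article*

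**What the plan says.** All references are to the protocol article.

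- **Questionnaires, before the procedure.** The items are described as follows: "Expectations include burden and pain of: the bowel preparation, intravenous cannula insertion, bowel insufflation, and the total procedure". They are answered "on a standard formatted 5-point scale (no pain, mild pain, moderate pain, severe pain, and very severe pain").
- **Questionnaires, after the procedure.** "Experience includes burden and pain of: the bowel preparation, intravenous cannula insertion, bowel insufflation, and the total procedure", answered "on standard formatted 5-point scale (identical to the pre-procedural form"). The purpose of this second form is given as: "This questionnaire is designed to assess the experienced burden and acceptability".
- **Questionnaires, worst aspect.** One item is described: "Which aspect of the procedure was most painful or burdensome".
- **Secondary objectives.** Pain and burden are named as separate quantities for six aspects and in total. A further objective is "The most painful and most burdensome aspect of CT colonography".
- **Statistical analysis.** Burden per aspect and total burden are compared by chi-square test. "Differences in the most burdensome aspect will also be calculated using the chi-square test". Expected burden is also a candidate covariate in the regression of pain scores.
- **Intervention.** The two forms have 22 and 17 questions. Their wording is not reproduced.

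**The concern.** Two things are to be rated, but the printed answer categories fit only one of them. A patient who found something a heavy burden without pain has no category that says so. The literal answer is the lowest one, no pain. Asking burden and pain in separate questions does not help if both are answered in grades of pain.

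The article gives burden its own objectives and tests. The Discussion expects a reduction in pain and burden together and links that to screening participation. If burden is scored in pain words, an effective analgesic will seem to lower burden simply because it lowers pain. The Background lists nausea and vomiting among the possible side effects of alfentanil. These are burdensome but not painful, so such a scale would credit the drug's benefit and miss part of its cost. The likely direction of error in the total rating therefore favours alfentanil.

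The worst-aspect item raises a related problem. Taken literally, one answer has to serve two outcomes. A patient for whom insufflation hurt most and preparation was the greatest burden could report only one of them.

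**Working it through.** There is no figure to reproduce, so the check sets the sections side by side and then counts items.

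**1. Labels against constructs.** Constructs assigned to the scale: two (burden, pain). Labels printed: five, from no pain to very severe pain. Labels that grade burden: none, here or elsewhere in the article. The post-procedural scale is declared identical, so both forms are covered.

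**2. What is affected.** The section lists three aspects plus the total, so 3 + 1 = 4 burden ratings per form and 4 × 2 = 8 over both forms. The four post-procedural ratings feed the chi-square tests. The pre-procedural ones supply the expected-burden covariate.

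**3. Where a between-arm distortion could arise.** The CT colonography section places preparation on the day before and the morning of the scan. The study drug goes in through the cannula already in place, before insufflation. Preparation and cannula insertion thus come before the drug, and no treatment effect on them is expected whatever the labels. Pain-worded labels could still misstate the level of burden for these aspects and weaken the covariate. Distortion of the comparison between arms would fall on insufflation and total burden.

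**4. Worst aspect in three sections.**

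| Section | What is named |
|---|---|
| Secondary objectives | most painful and most burdensome |
| Questionnaires | most painful or burdensome, described as one item |
| Statistical analysis | most burdensome, tested by itself |

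A test of the most burdensome aspect by itself requires that it be recorded separately, which the item as described does not do.

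**5. Does the form length settle the matter?** The post-procedural form has 17 questions.

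- Six aspects plus total, pain and burden asked separately: 7 × 2 = 14. Two worst-aspect questions and one on acceptance: 14 + 2 + 1 = 17.
- The same with a single worst-aspect question: 14 + 1 + 1 = 16.
- Only the items listed in the Questionnaires section: 4 × 2 + 1 + 1 = 10, or 11 with two worst-aspect questions.

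The first count matches. It is compatible with separate questions on the real form, but other sets of items could also add up to 17, and no count says anything about the answer labels.

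**The case against.** The strongest reply is that the article summarises forms it does not show. They are based on those of a previous trial, also not shown. The bracketed labels may merely illustrate the format, with parallel burden wording on the form itself. The Questionnaires section is visibly abbreviated: it rates three aspects plus the total where the objectives require six plus the total. The or in the worst-aspect item may be shorthand for two questions, which the count of 17 and the separate analysis of the most burdensome aspect both fit.

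Much of this stands. A reader might infer that the forms in use are defective, or that patients can in fact give only one worst-aspect answer; the article establishes neither. A reader might also count the absence of a stated test for the most painful aspect as an omission, but that can be left to the analysis plan. Nor does the article support the idea that bowel preparation is where the treatment comparison suffers most, since preparation precedes the drug.

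What does not fall away is the scale. The article chose to print the categories, assigned both burden and pain to them, and called the second form's scale identical. That is not detail left to a fuller document. It is a stated measurement rule that gives the wrong quantity if followed.

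**Conclusion.** The point holds for the measurement as described. The pain-only labels are the firm part. The worst-aspect wording is softer: the three sections do not agree, but the disagreement may be one of description only.

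The consequence is limited to secondary results: four burden ratings per form, the worst-aspect outcome and one regression covariate. For the treatment comparison, insufflation and total burden are the ratings that matter. A finding of lower burden there could not be told apart from the pain result. No numerical size can be given, because it depends on how closely pain and burden move together in these patients, and the article has no data on that.

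The conclusion assumes that the printed categories are those offered for the burden items. If the forms carry burden-worded categories, only the text is wrong. The primary outcome is collected verbally during the procedure on the 11-point NRS and is unaffected, so a reader should not extend the point to the main conclusion of the trial.

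**What to change.** First check the forms.

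- **If burden is answered in pain words,** give it five categories of its own on both forms, for example not, mildly, moderately, severely and very severely burdensome.
- **If there is one combined worst-aspect item,** replace it with two questions, one on the most painful aspect and one on the most burdensome, so that the questionnaire matches the secondary objectives and the planned analysis.
- **If the forms already do both,** correct the Questionnaires section to state the burden categories and to say that the worst-aspect questions are separate.

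The cost is rewording and at most one extra question, with no added visit or procedure. If data have already been collected on pain-worded burden items, report those results as such and do not present them as evidence on burden apart from pain.

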### Adverse events

Serious adverse event as defined by the ICH Guidelines for Good Clinical Practice E6 will be recorded and reported and mild adverse events, such as nausea will be recorded.

### Safety

An oxygen mask, an AMBU set, and naloxone will be available on site. The research physician, who prepares the study medication, will leave a signed sealed envelope (with patient name and patient number) with the given medication, which can be opened in case a serious adverse event occurs. The most serious adverse event caused by alfentanil within this setting is respiratory depression. The person administering alfentanil is trained in advanced life support; ensuring that this individual is competent in diagnosing respiratory depression and performing the appropriate treatment. In case of respiratory depression the patient will be ventilated, using a bagging bag with mask. Therefore oxygen, mask, and a bagging bag will be nearby.

To antagonize the induced respiratory depression 0.2-0.4 mg naloxone (B. Braun, Melsungen, Germany) will be given if necessary and can be repeated every 2-3 minutes. As extra precaution, a rescue plan has been created describing all steps that need to be performed in case of respiratory depression, hypotension, and bradycardia. The anaesthesiologists on call for emergency situations are informed about all CT colonography exams that will be performed.

### Recovery criteria

Each patient has to be observed by a blinded qualified staff member for one hour after the CT colonography procedure. For the monitoring of the recovery, the Aldrete score [31], a very commonly used score for recovery monitoring, is used at arrival at the recovery room and at 30 min and 60 min after alfentanil administration [Figure 2]. A score of 9 or higher obtained at 60 minutes is considered as ready for discharge and the participant may go home. If the score is lower than 9, another Aldrete score will be performed at 90 and 120 minutes. All scores will be recorded.

**Figure 2 F2:**
[figure not shown]
**Aldrete recovery criteria**.

### Statistical analysis

SPSS version 16.0 is used for all statistical calculations. A P value of 0.05 is defined as significant. Baseline characteristics are summarized with descriptive statistics. For categorical data the numbers or proportions are given, for normal distributed data the mean and standard deviation and for not normal distributed data the median with percentiles.

Differences between the alfentanil group and the placebo group will be tested for significance. For the calculation of differences in pain scores per position, average, and the maximum pain score during the procedure will be calculated using an independent samples t-test.

Differences in burden of different aspects of the procedure as well as the total procedural burden will be calculated using a chi-square test. Differences in the most burdensome aspect will also be calculated using the chi-square test. Differences in procedural time and recovery time will be calculated using an independent samples t-test.

We will test the associations between the baseline characteristics (independent variables mentioned below) and pain scores. As we consider the pain scores as continuous data, for this approach we will perform linear regression analyses.

Univariate analyses will be performed with pain scores as dependent variable and the following variables as independent variables: age, sex, BMI, education, ethnicity, expected burden, scan indication (including abdominal pain), known diseases and diagnosis, and whether it is the first CT colonography. Subsequently, the variables with a P value < 0.1 will be included in the multivariate analysis. In case more than four variables turn out to result in a P < 0.1, the four most influential variables will be used in the multivariate analysis. A stepwise backward selection strategy will be used, with a P value < 0.05 considered statistically significant.

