### Sample size

The sample size calculation was aimed at the detection of a difference in pain score between the alfentanil and placebo group. We calculated average pain score and standard deviation of a population screening trial performed in the AMC where the same insufflation procedure and 11-point NRS were used. The standard deviation was 2.6 in the pilot data. Based on our clinical experience with alfentanil we assume alfentanil will cause a reduction of 1.5 on an 11-point NRS. We tested this with a one-sided test, using 0.05 significance and 80% power. An independent samples t-test to compare means in two groups in nQuery Advisor 7.0, results in groups of 38 subjects. With an anticipated withdrawal rate of approximately 5%, we aim to include 45 patients per group.

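### Burden is scored on an ordered 5-point scale but compared with a chi-square test that ignores the order: valid, but inefficient for a consistent shift in a secondary outcome

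*Protocol article*

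**What the plan says.** The Questionnaires section has patients rate the burden and pain of several aspects, and of the total procedure, on a 5-point scale. The same format is used before and after the procedure. The printed labels are "no pain, mild pain, moderate pain, severe pain, and very severe pain". They are worded for pain only. That burden uses an equally ordered set is a fair inference from the shared format, not something the text spells out.

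The Statistical analysis section then fixes the test: "Differences in burden of different aspects of the procedure as well as the total procedural burden will be calculated using a chi-square test". The next sentence gives the same test to an item whose answers have no order: "Differences in the most burdensome aspect will also be calculated using the chi-square test". No trend version, rank test or merging of categories is named, so the ordinary Pearson test is the natural reading for both.

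Burden is listed under Secondary objectives. The Discussion states that a clinically relevant fall in pain and burden is expected.

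**The concern.** Shuffling the five columns of a 2×5 table leaves the Pearson statistic and its p-value unchanged. The test therefore asks whether the two distributions differ in any way, while the trial asks whether burden is lower with alfentanil. There are two consequences. A consistent downward shift is spread over 4 degrees of freedom, which costs power. A significant result also does not say which way burden moved.

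At stake is the reading of one secondary outcome. It matters because the Discussion links lower burden to participation in screening, and a null result from an inefficient test could be taken as no effect on burden.

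**Working it through.** **Inputs from the article (Sample size).** Assumed reduction 1.5 NRS points, SD 2.6, one-sided 0.05, 80% power, 38 per group calculated, 45 per group enrolled, about 5% withdrawal. With 5% withdrawal, 45 × 0.95 = 42.75, so about 43 per group remain.

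**Plan's own figure.** n = 2 × [(1.645 + 0.842) × 2.6/1.5]² = 37.2, rounded up to 38 per group. This reproduces, but it concerns pain on the NRS. No power, effect size or expected distribution is given for burden.

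**Assumptions added here.** (a) Burden shifts by the same standardised amount as pain, d = 1.5/2.6 = 0.577. (b) Tests are two-sided at 0.05; the Statistical analysis section says only "A P value of 0.05 is defined as significant".

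**Step 1: same signal on 1 or 4 degrees of freedom.** The noncentrality is λ = (n/2) × d². The critical values are 3.84 (1 df, ordered test) and 9.49 (4 df, Pearson).

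| n per arm | λ | Ordered, 1 df | Pearson, 4 df | Gain |
|---|---|---|---|---|
| 45 | 22.5 × 0.333 = 7.49 | 78.1% | 57.2% | 20.9 points |
| 38 | 19 × 0.333 = 6.32 | 71.0% | 49.3% | 21.7 points |

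**Step 2: simulated 5-level data.** Six assumed placebo distributions, from an even spread to a strong floor, were shifted by d = 0.577, with 20,000 trials each. Wilcoxon with tie correction gained 23 to 25 points over Pearson at 45 per arm and 22 to 24 at 38 per arm. Examples at 45 per arm: even spread 71.9% against 48.7%; floor 56.4% against 33.1%.

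**Step 3: other effect sizes.** For one assumed placebo distribution (0.15, 0.30, 0.30, 0.18, 0.07), 43 per arm, the odds of a lower category were multiplied by a common odds ratio (OR):

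| OR | Pearson | Wilcoxon | Gain |
|---|---|---|---|
| 1.5 | 10% | 18% | about 7 points |
| 2 | 24% | 42% | 18 |
| 2.5 | 41% | 64% | 24 |
| 3 | 57% | 80% | about 22 to 23 |
| 4 | 80% | 94% | 14 |
| 5 | 91% | 98% | about 8 |

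Over the six distributions at 45 per arm, the gain was 7 to 8 points at OR 1.5, 16 to 19 at OR 2, 21 to 24 at OR 2.5 and 21 to 23 at OR 3. Where Wilcoxon has 90% power, it was 16 to 18 points.

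**Step 4: sparse cells.** With equal arms, each expected count is half the category total, so any category with fewer than 10 patients overall has expected counts below 5. At 45 per arm, some expected count fell below 5 in 4% to 30% of trials with an even spread, in 85% to 94% with a bell-shaped spread, and in practically all trials with the other four. Under no effect, Pearson still rejected in only 3.5% to 4.9% of trials.

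**Step 5: shifts that are not proportional.** With the placebo distribution of Step 3 and 43 per arm, moving most severe and very severe answers to moderate only (0.15, 0.30, 0.48, 0.06, 0.01) gave Pearson 47% and Wilcoxon 14%. A gain concentrated in the lowest category (0.40, 0.15, 0.22, 0.16, 0.07) gave about 60% against 33%.

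**The case against.** The strongest reply is that the chi-square test is a valid test of whether the groups differ, applied to a secondary outcome for which the trial was not sized. Most of this stands.

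- **Size of the loss.** A reader might infer that chi-square always costs more than 20 points here. The documents do not support that, because they give no burden effect. The figure holds around the planning effect and shrinks on either side of it (Step 3).
- **Pattern of effect.** Proportional shifts favour rank tests. Step 5 shows that one-directional but strongly non-proportional shifts can reverse the ranking. An ordered test is therefore not free of cost.
- **Sparse cells.** A reader might infer that small expected counts make the test unsafe. They depend on a distribution that is not given, and where they occur the test becomes slightly conservative. False positives do not increase.
- **Reach.** Bowel preparation and cannula insertion come before the study drug, so little effect, and hence little loss, is expected there. The point bears mainly on insufflation, later aspects and total burden.
- **Pain items.** A reader might extend the point to the 5-point pain ratings. The Statistical analysis section names chi-square for burden and for the most burdensome aspect, not for those ratings.

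The objection does not remove the mismatch: the expectation for burden is directional, the scale is ordered, and the chosen test uses neither.

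**Conclusion.** The point holds as an efficiency problem in a secondary analysis. The article assigns an order-blind test to an ordered outcome for which it expects a reduction. If burden shifts consistently by the planning effect for pain, an ordered test gains about 21 to 25 percentage points of power. That rests on a borrowed effect size, assumed distributions and two-sided testing at 0.05. The gain is about 7 points for a small effect (OR 1.5) and 14 for a large one (OR 4), and it can be negative for strongly non-proportional differences. It would go too far to call the chi-square test invalid or its type I error inflated. The primary comparison of maximum pain and its sample size are untouched. This is a cheap improvement, not a defect that threatens the trial.

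**What to change.** In the Statistical analysis section, replace the chi-square test for the 5-point burden items and total burden with one named ordered test, either Wilcoxon-Mann-Whitney with tie correction or linear-by-linear trend. For example:

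> Burden of each aspect and of the whole examination will be compared between groups with the Wilcoxon-Mann-Whitney test, corrected for ties, and the number of patients in each category will be shown by group. The aspect named as most burdensome will be compared with the chi-square test.

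The category counts let a reader see a non-monotone or strongly non-proportional difference, for which the ordered test is weaker. If a common odds ratio is reported as well, state that it assumes proportional odds. Fix the choice before unblinding so that it does not depend on the results.

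The cost is about one sentence, with the same data and software. The one trade-off is the lower power for the patterns in Step 5 of the working.

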During conventional colonoscopy administration of analgesics is standard. To the best of our knowledge, no analgesic is administered during CT colonography. To induce sufficient analgesia during CT colonography an opioid will be necessary. Studies using preventive oral analgesic agents for acute pain often do not result in a significant pain reduction [14-17]. In colonoscopy opioids are routinely used, often in combination with a benzodiazepine because of the synergetic effect [18,19]. CT colonography is expected to be less painful compared with colonoscopy without the administration of analgesic medication. A benzodiazepine as co-medication is therefore probably not required. Because of a procedural time of about 20 minutes a short acting opioid like fentanyl or alfentanil will be sufficient and thus prevents long recovery times [20-22]. An opioid bolus has been shown to improve pain scores during sigmoidoscopy [23]. Alfentanil has the advantage of being one of the most short-acting opioids and with the shortest recovery time [20-22]. The need for recovery facilities could have detrimental consequences on the clinical use as well as for CT colonography as a screening tool and this favours alfentanil [24].

Alfentanil is a relatively safe drug, but has possible side effects like other opioids such as: nausea, vomiting, hypotension, bradycardia and respiratory depression. However, in low- to medium-dose and without the use of a benzodiazepine, the incidence respiratory depression is extremely low [20,22,25,26]. In a study of Cho et al. a bolus injection of 10 μg/kg alfentanil did not induce any hypoxemia, desaturations or apnoeas [26].

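### Recovery time is known only to the interval between scheduled Aldrete checks, so a t-test on minutes gives a mean difference that depends on when the checks fall

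*Protocol article*

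**What the plan says.** Three sections of the protocol article together fix this outcome.

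- **Time** sets the end point: "The end of recovery is defined as the time that the first Aldrete score of 9 or higher is measured". It also sets the interval: "the time from the start of the procedure until the end time of recovery is noted".
- **Recovery criteria** sets when a score can be measured. The Aldrete score "is used at arrival at the recovery room and at 30 min and 60 min after alfentanil administration". For a patient not ready at 60 minutes: "If the score is lower than 9, another Aldrete score will be performed at 90 and 120 minutes". No later score is scheduled.
- **Statistical analysis** sets the comparison: "Differences in procedural time and recovery time will be calculated using an independent samples t-test". The significance level is general to the section: "A P value of 0.05 is defined as significant".

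Procedure and recovery time are listed among the secondary objectives. The Background gives short recovery as a reason for choosing alfentanil, and the Discussion expects pain relief without a cost in recovery time.

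**The concern.** The definition, the schedule and the test are all stated, and they do not fit together well. A patient who reaches 9 between two checks is recorded at the later one. A patient who has recovered before reaching the recovery room is recorded at arrival. A patient below 9 at the last check has no end of recovery under the definition, and a t-test cannot use a missing time. The t-test nevertheless treats every recorded time as an observed duration.

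What is at stake is the meaning of the recovery result. Quick recovery is part of the case for alfentanil, so the reported difference in minutes will be read as the delay that the drug causes. It could be well below or well above that delay. A non-significant difference could also be read as support for the expectation of no recovery cost.

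**Working it through.** **Inputs from the protocol article**
- Checks on arrival and at 30, 60, 90 and 120 minutes (Recovery criteria).
- Procedural time of about 20 minutes (Background).
- 45 patients per group and about 5% withdrawal (Sample size), so 45 × 0.95 = 42.75, or about 43 evaluable per group.

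The article gives no mean, SD, difference or power for recovery time. Its only sample size figure concerns pain: SD 2.6, difference 1.5, one-sided 0.05 and 80% power. That reproduces (37.85, so 38 per group) but says nothing about recovery.

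**Assumptions not in the article**
- Arrival at about 20 minutes after injection (SD 4).
- Lognormal true recovery times.
- Where time is counted from procedure start, about 8 minutes (SD 3) from start to injection.
- Two-sided testing at 0.05.

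**Step 1: width of the intervals.** 60 − 30 = 90 − 60 = 120 − 90 = 30 minutes. Each gap exceeds the whole procedure of about 20 minutes.

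**Step 2: recorded against true mean difference.** A lognormal mean is median × exp(log-SD²/2). With log-SD 0.5 the factor is exp(0.125) = 1.133.
- Medians 5 v 10: true difference (10 − 5) × 1.133 = 5.7 minutes; recorded on the schedule, 1.7. About 89% of alfentanil patients have then recovered before arrival.
- Medians 5 v 15: true (15 − 5) × 1.133 = 11.3 minutes; recorded, 6.1. About 69% have recovered before arrival.
- The opposite direction: 10% of alfentanil patients recover at 31 minutes, and all others at arrival (20 minutes). True extra mean 0.10 × (31 − 20) = 1.1 minutes; recorded 0.10 × (60 − 20) = 4.0.

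**Step 3: type I error.** With identical distributions in both arms (45 per arm, 20,000 simulated trials), the t-test on scheduled times rejected in 4.8 to 4.9% of trials.

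**Step 4: power lost to the schedule itself.** This compares a t-test on exact times with a t-test on scheduled times (45 per arm, assumed true means in minutes after injection, coefficient of variation 0.4).
- 10 v 14: 92% falls to 30%.
- 20 v 25: 70% falls to 57%.
- 20 v 30: 99.5% falls to 98%.

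This information was never collected, so no analysis of the same data recovers it.

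**Step 5: t-test on recorded minutes against an exact (permutation) rank test on the check category** (43 per group). Ranges reflect how much procedure and transfer variation is included.

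| Scenario | t-test | Rank test |
|---|---|---|
| First pass at arrival/30/60: 98/2/0% v 80/15/5% | 42–53% | 74–77% |
| First pass at arrival/30/60: 95/5/0% v 70/25/5% | 62–73% | 86–88% |
| Lognormal medians 5 v 10, from injection | 28% | 29% |
| Lognormal medians 5 v 10, from procedure start | 23% | 31% |
| Lognormal medians 20 v 25 | 40–42% | 42–43% |
| Lognormal medians 20 v 30 | 90% | 90% |
| All at arrival, except 10% of alfentanil patients at 60 | 37–49% | 26–31% |

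The last row can be checked directly. With no late patient on placebo, Fisher's exact p is 0.055 for 5 late alfentanil patients and 0.026 for 6. At least 6 of 43 are therefore needed, and the binomial probability of that at 10% is 26%.

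**The case against.** The strongest reply is that the endpoint is coherent as written. It is the time at which a passing score is measured, not the moment of physiological recovery. Both arms share one schedule and a blinded observer, so the comparison is fair and the type I error is sound. That stands. It does not make the mean difference an estimate of delay, and the clinical argument in the Background and Discussion is about delay.

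Four stronger readings are tempting, and the documents do not support them.

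- *The t-test generally loses power to a rank test.* It does not. The gain is clear when most patients pass on arrival and some alfentanil patients first pass at 30 minutes. It vanishes when recovery spreads over several checks. It reverses when a few patients are recorded at 60, because ranks ignore how late they are.
- *Changing the test removes the dependence on the schedule.* It does not. Categories defined by the checks are just as coarse. They only report the coarseness openly.
- *Slow patients will be excluded.* The article states no exclusion and says that all scores are recorded. Handling of such patients may be settled in an analysis plan not shown. What the article does establish is that its definition gives them no value. They may also be very rare: with a median of 15 minutes and log-SD 0.5, about 0.002% exceed 120 minutes.
- *The trial's main conclusion is at risk.* The primary pain comparison and the sample size are untouched.

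**Conclusion.** The point holds as one about interpretation. On the article's own definition and schedule, recovery time is interval-censored, with gaps of up to 30 minutes. For anyone recovered on arrival it is mostly procedure and transfer time, and it is undefined for anyone below 9 at 120 minutes. This is so whichever starting point the interval has. The mean difference from the t-test can be less than a third of the true delay (1.7 against 5.7 minutes) or more than three times it (4.0 against 1.1).

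Those sizes, and every power figure, rest on assumed recovery distributions and an assumed arrival time, because the article gives none. The false-positive rate is not affected, and no general claim about power is justified. Severity is minor to moderate, for a secondary outcome only.

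**What to change.** In the Statistical analysis section, keep the t-test for procedural time and replace it for recovery time.

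- Classify each patient by the first assessment with an Aldrete score of 9 or higher: arrival, 30, 60, 90, 120, or not by 120 minutes as the worst level.
- Compare the arms with an exact rank-sum or trend test.
- Report the percentage recovered at each check in each arm, with 95% CIs.
- If a figure in minutes is wanted, use an interval-censored estimate.

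This costs a few sentences of wording and needs no new data, because all scores are already recorded. It also gives every patient with recorded scores a defined outcome. The price is that there is no longer a single mean difference in minutes, and some power is lost if the drug's effect is a few very late recoveries. The information lost to the coarse schedule is not regained; only more frequent scoring would do that.
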